### Statistical Analysis

#### Primary Analysis

The predictive plasma profile of metastatic relapse will be investigated using an approach based on the elastic-net method. Firstly, univariate analyses (Wilcoxon-Mann-Whitney tests with *p*-value correction for FDR control) will be performed to evaluate the relationship between the concentration of each protein and the occurrence of relapse. Then, a multivariate logistic regression model with elastic-net regularization will be constructed to allow an intrinsic selection of predictive variables (proteins). If necessary, a selection stabilization algorithm will also be applied. The results of the analysis will therefore be the set of predictive variables selected by the selected model, their regression coefficients, as well as an estimation of the model performance (with associated confidence intervals). However, in the absence of a test dataset the performance of the model can only be estimated by cross-validation.

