## Methods and Study Design

### Study Design

This is a single-centre prospective trial designed to evaluate a plasma protein profile as a predictive biomarker for metastatic relapse of TNBC. The estimated duration of patients’ enrolment is 3 years: 90 patients will be enrolled and followed from the patient inclusion until the first metastatic relapse or up to 5 years after the end of treatment if no relapse occurs. Study design is presented in **Figure 1**. TNBC patients will have blood samples taken at diagnosis, on the day of first-line surgery or post-NAC surgery, on the day of radiotherapy start, and 6 months and one year after the end of radiotherapy. Patients receiving neoadjuvant radiation will not be included in the trial. In case of recurrence, a blood sample will be taken at the time of diagnosis of metastatic relapse. Blood samples will be used for the quantification of plasma proteins, for the determination of blood cells and for the quantification of ctDNA. TILs rate evaluation will be performed on tumour tissue from the biopsy and from the operating specimen. The quantification of proteins will be done by multiplex ELISA. The identification of tumoral DNA mutations will be made from extracted DNA from tumour tissue from the operating specimen or from the biopsy. All coding regions, including exons borders and splicing sites, of the ten most frequently muted genes in breast tumours (including TP53, PTEN, PIK3CA, etc) will be captured from sample genomes. Then, targeted regions will be analysed by high throughput sequencing. Targeting several genes will ensure to discover at least one tumour-specific mutation. This mutation will later be quantified in peripheral blood samples. The RNA signature will be generated from transcripts extracted from tumour tissue from the surgical specimen or from the biopsy. A multiplex RT-qPCR will quantify the expression levels of the 6 genes of interest. The expression level of each gene will be multiplied by the corresponding coefficient in order to generate a prognostic score.

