### Study Objectives

The primary objective of the INSTIGO trial is to discover a baseline plasma protein profile predictive of metastatic relapse in patients with TNBC (**Table 1**). It also aims to identify a plasma protein profile at different times during patient follow-up that could be predictive of metastatic relapse. Based on a review of the literature INSTIGO focuses on a specific group of proteins: Matrix metalloproteinase 9, tissue inhibitor of metalloproteinase 1, interleukin-6, interleukin-8, interleukin-10, programmed death-ligand 1, stromal cell-derived factor 1, GM-CSF, tyrosine kinase with immunoglobulin and epidermal growth factor-homology domains 2, TGF-β, VEGF-A, hepatocyte growth factor, fibroblast growth factor, CXCL5, CXCL12. Moreover, the INSTIGO study takes interest in others potential biomarkers such as ctDNA, blood cells, TILS, or tumour RNA expression (**Table 1**). Briefly, the objective is to evaluate the ability of those potential biomarkers to predict metastatic relapse in patients with triple-negative breast cancers.

**Table 1 T1:** Primary and secondary objectives.

Primary objective	To discover a baseline plasma protein profile predictive of metastatic relapse in patients with TNBC
Secondary objectives	To discover plasma protein profiles predictive of metastatic relapse in patients with TNBC, assessed at - the day of first surgery or post-CTNA surgery - the day of the radiotherapy start - 6 months and one year after radiotherapy
	To study the relationship between the quantity of tumour infiltrating lymphocytes at diagnosis and metastatic relapse
	To study the relationship between NLR and PLR and metastatic relapse, when those 2 parameters are assessed at - diagnosis - the day of first surgery or post-CTNA surgery
	To study the relationship between plasma levels of circulating tumoral DNA and metastatic relapse - at diagnosis - at the day of first surgery or post-CTNA surgery - at the day of the start radiotherapy start - 6 months and one year after radiotherapy
	To verify prognostic value of a baseline RNA signature
In neoadjuvant setting	To identify a baseline plasma protein profile predictive of histological response to neoadjuvant chemotherapy (NAC)
	To study the relationship between variation in protein concentration, between diagnosis and end of NAC, and histological response to NAC

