### Recruitment and Consent

Eligible patients will be offered the opportunity to participate in the study by their oncologist or their surgeon. Patients who agree to participate in this study will provide written informed consent for enrolment. Data obtained will be retained with consent, and any reasons given for withdrawal will be recorded. Participants can withdraw at any time.

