### Sample Size Calculation

Given the exploratory nature of the study, and the lack of sufficient data to provide hypotheses in order to perform sample size calculation, the objective is to recruit a maximum of patients. The recruitment capacity for this study is estimated at 90 patients (30 patients per year). An interim analysis at 30 patients will allow us to re-evaluate the recruitment capacity, and to assess the interest of extending the recruitment period, and to re-estimate the number of subjects needed in view of the amount of missing data and the variability of the protein data. A rough estimation allows us to evaluate that with a sample size of 90 patients we would obtain a 95% (Wilson’s) confidence interval for the sensitivity of a 90% predictive score, with a precision of +/- 12%, assuming that the proportion of metastatic relapses at 5 years will be 1/3.

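### The primary analysis treats metastatic relapse as yes/no with no stated horizon, although the design yields event times with unequal follow-up; a penalised Cox model would use the data better at almost no cost

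*Protocol article*

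**What the plan says.** The primary objective (Study Objectives) is "to discover a baseline plasma protein profile predictive of metastatic relapse in patients with TNBC".

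- **Method.** Under Primary Analysis, Mann-Whitney tests with FDR correction are used "to evaluate the relationship between the concentration of each protein and the occurrence of relapse". After that, "a multivariate logistic regression model with elastic-net regularization will be constructed to allow an intrinsic selection of predictive variables (proteins". Both need a two-valued outcome. No time-to-event method appears there or under Secondary Analysis, which reuses the same approach for profiles at later time points.
- **Follow-up.** Under Study Design, patients are "followed from the patient inclusion until the first metastatic relapse or up to 5 years after the end of treatment if no relapse occurs".
- **Withdrawal.** Recruitment and Consent states: "Participants can withdraw at any time". No expected rate of loss is given.
- **Horizon.** A fixed horizon appears only under Sample Size Calculation, where precision is worked out "assuming that the proportion of metastatic relapses at 5 years will be 1/3". Primary Analysis does not adopt it as the outcome definition.

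**The concern.** The follow-up rule produces a time to relapse for some patients and a censoring time for the rest. Censoring times will differ because treatment lengths differ and because patients can leave early. A yes/no outcome has no place for a patient observed relapse-free for, say, two years and then lost: she must be called a non-relapser or left out. It also treats a relapse in the first year and one in the fifth as the same event.

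This matters because relapses are the scarce resource. About 30 are expected, and they must support selection among some fifteen candidate proteins. The article concedes that there is no separate test dataset, so performance can be estimated only by cross-validation. Power lost at the selection step, or proteins selected because they track drop-out, would not be caught later within this study.

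**Working it through.** **1. The plan's own figure.** Inputs from Sample Size Calculation: N = 90, relapse proportion 1/3, sensitivity 90%, 95% Wilson interval. Relapsers = 90 × 1/3 = 30; detected = 0.9 × 30 = 27.

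- Centre = (0.9 + 1.96²/60) / (1 + 1.96²/30) = 0.855
- Half-width = 1.96 × √(0.09/30 + 1.96²/3600) / (1 + 1.96²/30) = 0.111
- Interval: 74.4% to 96.5%

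The stated ±12% agrees with this as the rough estimate it is called (Clopper-Pearson gives 12.2 points, continuity-corrected Wilson 12.5). It assumes that all 30 relapses are observed. It is not in dispute here.

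**2. What loss does to a yes/no outcome.** Assumptions: constant relapse hazard λ = −ln(2/3)/5 = 0.0811 per year; independent exponential loss with hazard μ = −ln(1 − L)/5, where L is the cumulative loss by year 5. The documents give no L, so a range is shown.

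Proportion observed to relapse = λ/(λ+μ) × [1 − (2/3)(1 − L)]. For L = 20%, μ = 0.0446, so the proportion is 0.645 × 0.467 = 0.301, or 27.1 of 90. Patients lost before any relapse: 0.355 × 0.467 = 0.166, or 14.9 of 90. Relapses missed: 30 − 27.1 = 2.9. Relapse proportion if the lost are dropped: 0.301/(1 − 0.166) = 36.1%.

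| Loss by year 5 | Lost without relapse (of 90) | Relapses missed | Proportion if coded non-relapse | Proportion if dropped |
|---|---|---|---|---|
| 5% | 3.7 | 0.7 | 32.5% | 33.9% |
| 10% | 7.4 | 1.4 | 31.7% | 34.6% |
| 20% | 14.9 | 2.9 | 30.1% | 36.1% |
| 30% | 22.5 | 4.5 | 28.4% | 37.8% |

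The target is 33.3%. The two binary conventions err in opposite directions; an analysis that handles censoring aims at the target.

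**3. Power for one protein.** Simulated cohorts of 90 (3,000 to 4,000 per scenario, repeated), hazard ratio 1.6 per SD, 1/3 relapsing at 5 years, 5.75-year window, two-sided 5% without FDR correction. Ranges are over repeat runs.

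| Loss | Mann-Whitney, lost coded non-relapse | Cox |
|---|---|---|
| none | 71–73% | 76–78% |
| 10% | 69% | 74% |
| 20% | 63–67% | 70–73% |
| 30% | 61–64% | 69–70% |

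The gap is about 5 points with no loss and about 5 to 7 points at 10 to 30% loss (one run at 30% gave 8). Dropping the lost patients does not recover it: 65% at 20% loss and 61% at 30%, the same as coding them in that run.

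**4. False positives when loss depends on the protein.** No true effect on relapse, nominal 5%. At 10% loss the rate is about 5% (up to 6% when the hazard of loss doubles per SD). At 20% loss it is 7 to 10% if lost patients are coded as non-relapsers and 6 to 7% if dropped. Cox stays at about 5 to 6%.

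**5. The follow-up window.** Observation ends 5 years after treatment, not 5 years after inclusion. If treatment lasted 6 or 12 months (assumed), expected relapse is 1 − exp(−0.0811 × 5.5) = 36.0% or 1 − exp(−0.0811 × 6.0) = 38.5%. The difference is small.

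**The case against.** The other side has real substance.

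- **A binary outcome is legitimate.** At a common 5-year horizon with complete follow-up, logistic classification is valid and matches the planned sensitivity estimate. A patient who completes the follow-up rule without relapse has known 5-year status. This stands. What remains is that Primary Analysis does not name the horizon and that follow-up need not be complete.
- **A reader might infer that lost patients and those who die without metastasis count as non-relapsers.** The article does not say so. Exclusion is equally possible, and the rule may sit in a full protocol or analysis plan that is not shown. That silence is not the finding. The finding is the stated choice of method, which is weaker under either rule.
- **A reader might call a death without metastasis a misclassified relapse.** It is not: that patient never had a metastatic relapse. Death is a competing event whose place in the outcome has to be defined.
- **A reader might expect serious false selection.** Rates of 13% or more can be simulated, but they need a strong association between protein and loss. At a nominal 20% loss, a loss hazard ratio of 1.5 per SD gives about 6% and one of 3 per SD gives 16%. Nothing in the documents supports the stronger values.
- **Discrimination hardly moves.** With a hazard ratio of 2 per SD, the 5-year AUC falls from 0.719 to 0.711 at 20% loss if lost patients are coded as non-relapsers, and does not fall if they are dropped.
- **The study is exploratory.** This lowers the stakes but is no reason to discard event times that follow-up provides anyway.

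**Conclusion.** The point holds in limited form. The article fixes a yes/no primary analysis without a horizon for data that are event times with unequal follow-up. The cost is about 5 points of power with full follow-up and about 5 to 7 points at 10 to 30% loss, plus a mild excess of false positives if loss is related to the protein. Much of the power gap is present with no loss, so it mainly reflects unused event times, not miscounted patients.

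These sizes rest on assumed values: a hazard ratio of 1.6 per SD, constant and proportional hazards (which suit Cox), and loss rates that the documents do not give. They concern the single-protein tests; the elastic-net step was not simulated. The window effect is minor and would not justify a change alone. This is a worthwhile, cheap improvement that should be made, not a flaw that must be cured before the study can be interpreted.

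**What to change.** In Primary Analysis:

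1. Define the primary outcome as time from inclusion to first metastatic relapse, censored at the last disease assessment, with death without metastasis as a competing event (cause-specific hazard).
2. Replace the Mann-Whitney screen with univariable Cox tests under the same FDR control.
3. Replace the logistic elastic-net with an elastic-net Cox model, retaining the planned stabilisation and cross-validation.
4. Report sensitivity and specificity at a fixed 5 years from inclusion with inverse-probability-of-censoring weights. This keeps the link to the sample-size statement.
5. Keep the logistic elastic-net as a sensitivity analysis in patients with known 5-year status.

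The cost is analysis wording: no new patients or samples, only the date of relapse or last assessment, and Trial Status reports just 2 patients recruited. The downsides are that coefficients become log hazard ratios and that the interval for 5-year sensitivity is slightly wider.

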#### Secondary Analysis

To identify a plasma protein profile that is predictive of metastatic relapse, the same approach as for the main objective will be used.

The relationship between TILs, NLR and PLR levels measured at different times, or ctDNA plasma levels and metastatic relapse will be studied by Wilcoxon-Mann-Whitney tests and logistic regressions. Mixed models will be used to account for repeated data.

The relationship between, on the one hand, the variation in protein concentration, the variation in TILs, or the variation in PLR and NLR levels, between diagnosis and end of NAC, and, on the other hand, the histological response to NAC, will be studied as in the previous point. These aspects are also concerned by an intermediate analysis on the first 30 patients.

An RNA signature predictive of metastatic relapse will be assessed by applying a previously constructed model on the data obtained in the INSTIGO study. The classical indices for the evaluation of a classification (sensitivity, specificity, and precision, among others) will be calculated.

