	To study the relationship between TIL quantity before and after NAC, as well as between the relationship between the baseline TIL level and the level of histological response to NAC
	To study the relationship between the variation of the PLR ​​and the NLR before and after NAC, as well as between the relationship between the baseline PLR and NLR levels and the level of histological response to NAC

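### The analyses of marker change during NAC name no adjustment for the marker's baseline value, so an association with histological response may reflect the starting level rather than the change

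*Protocol article*

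**What the plan says.** Under Secondary Analysis, the exposure is "the variation in protein concentration, the variation in TILs, or the variation in PLR and NLR levels, between diagnosis and end of NAC" and the outcome is histological response. The method is given by reference: "the histological response to NAC, will be studied as in the previous point". The previous point, on TILs, NLR, PLR and ctDNA against relapse, reads "will be studied by Wilcoxon-Mann-Whitney tests and logistic regressions. Mixed models will be used to account for repeated data". No covariate is listed for these models, and none is excluded.

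Table 1 words the protein objective as "To study the relationship between variation in protein concentration, between diagnosis and end of NAC, and histological response to NAC". In the same neoadjuvant block, baseline levels are set against response as separate objectives: the baseline protein profile, "the baseline TIL level and the level of histological response to NAC" and "the baseline PLR and NLR levels and the level of histological response to NAC".

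The Introduction cites a link between baseline level and response for one of these markers: TNBC patients with a raised NLR respond less well to NAC. The change analyses are also to be looked at after the first 30 patients. The article does not say how many of the 90 planned patients will receive NAC.

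**The concern.** A change score contains the starting value with a minus sign. Unless follow-up tracks baseline one for one, patients who start high tend to fall and patients who start low tend to rise. If the starting level is related to response, the change is then related to response as well, even when what happens during NAC carries no further information.

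NLR shows how this could go. Suppose a high NLR at diagnosis goes with poor response, as the Introduction reports, and NLR regresses towards the mean. Patients with high NLR then tend both to fall and to respond poorly, so a falling NLR would look unfavourable. The same mechanism can hide a real effect of change that runs in the same direction as the baseline effect.

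What is at stake is attribution. A result could be reported as a finding about change on treatment when it restates the baseline finding with its sign reversed. Analysing baseline in a separate objective shows that a baseline effect exists, but does not remove it from the change analysis.

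**Working it through.** **Plan's own figure.** There is none for this point. The only precision figure in the article concerns the sensitivity of a relapse score and does not enter here.

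**Inputs.** From the article: the exposure, the outcome, the named methods, the planned total of 90 and the look at 30 patients. Assumed, because the article gives no values: number of NAC patients, response rate, within-patient correlation, ratio of follow-up to baseline SD, and size of the baseline effect. Variation is taken as the simple difference, which the article does not define.

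**Step 1: link between change and baseline.** Let B be the baseline value, F the end-of-NAC value and b the slope of F on B. Then cov(F − B, B) = (b − 1)·var(B), which is negative when b < 1 and zero when b = 1. With equal variances and correlation r, b = r and

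corr(F − B, B) = −(1 − r)/√(2(1 − r)) = −√((1 − r)/2).

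This gives −0.59 at r = 0.3, −0.50 at r = 0.5 and −0.39 at r = 0.7.

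**Step 2: effect on the group comparison.** If responders differ by d SD at baseline and F depends on response only through B, mean change differs between the groups by (b − 1)·d. At b = 0.5 and d = 0.8 this is −0.4 SD, opposite in sign to the baseline difference.

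**Step 3: how often the tests reject, with a baseline odds ratio per SD.** Equal variances, no effect of change given baseline, two-sided 5%, 1,500 trials per setting:

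| NAC patients | r | Odds ratio | Wilcoxon | Logistic, change only | Logistic, change + baseline |
|---|---|---|---|---|---|
| 60 | 0.5 | 2.0 | 19.5% | 19.0% | 3.5% |
| 60 | 0.3 | 2.5 | 39.4% | 38.7% | 4.3% |
| 45 | 0.3 | 2.5 | 31.3% | 30.7% | 5.1% |

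At the mild end (60 patients, r = 0.7, odds ratio 1.5), a run of 1,000 trials gave about 8%, 7% and 5%. Repeating the first row gave about 22% unadjusted and 4% adjusted, so run-to-run differences of a few points should be expected. In the r = 0.5, odds ratio 2 and r = 0.3, odds ratio 2.5 settings, at least 99% of the significant unadjusted logistic results had the sign opposite to the baseline effect.

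**Step 4: a second parameterisation, and the limits.** Baseline shifted by d SD in responders, response rate 40%, 1,000 trials per setting. With normal values and equal variances the odds ratio per SD is exp(d): 1.65 for d = 0.5 and 2.23 for d = 0.8. For 60 patients and d = 0.8:

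| r | SD ratio F/B | Slope b | Wilcoxon | Logistic, change only | Logistic, change + baseline |
|---|---|---|---|---|---|
| 0.3 | 1 | 0.3 | 39.2% | 40.9% | 4.7% |
| 0.5 | 1 | 0.5 | 28.5% | 27.3% | 5.1% |
| 0.7 | 1 | 0.7 | 17.5% | 17.0% | 4.4% |
| 0.9 | 1 | 0.9 | 11.6% | 11.0% | 6.3% |
| 0.7 | 1.43 | 1.0 | 4.1% | 3.6% | 4.1% |
| 0.5 | 2 | 1.0 | 4.0% | 3.7% | 4.0% |

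With 30 patients and d = 0.8, the ranges over r = 0.9 to 0.3 are 7% to 23% (Wilcoxon) and 5% to 20% (logistic, change only). If all 90 patients received NAC they would be 13% to 56% and 14% to 57%. With d = 0 and 60 patients the rates are 6.7%, 5.5% and 5.8%. Adjusted rates lie between about 3% and 7% throughout.

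**Step 5: what the adjusted coefficient means.** a + β₁(F − B) + β₂B = a + β₁F + (β₂ − β₁)B. So β₁ is the effect of the end-of-NAC value given the baseline value.

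**The case against.** Three objections have force.

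*Silence is not exclusion.* A reader might infer that the change analyses leave baseline out altogether. The article does not say so. Logistic covariates are neither listed nor ruled out, mixed models are also named, and the full protocol is not shown. This stands against any statement that the whole analysis is unadjusted. It does not rescue the Wilcoxon test, which cannot adjust, and nothing in the article says which result carries the conclusion. A mixed model does not by itself condition on baseline either.

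*The unadjusted test is valid for its own question.* The objective is worded as a relationship, and in these simulations mean change really does differ between responders and non-responders (step 2). The rejections are therefore not errors of the Wilcoxon test as a test of marginal association. The 5% yardstick belongs to the null of no effect given baseline. This also stands. The error would lie in crediting the association to the change.

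*The effect is not inevitable.* A reader might infer that a baseline-only marker will show up as a change effect. In most simulated trials with 45 to 60 patients it does not, and at slope 1 there is no excess. Nor does the article state that it expects baseline associations for every marker. Listing an objective is not an expectation, and only NLR has such a link cited.

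Finally, the analysis is exploratory and secondary, and baseline results would be reported beside it. That limits the consequence but does not separate change from starting level.

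**Conclusion.** The point holds in a limited form. The article names an unadjusted test of change and logistic models with no stated baseline term, so a reported change-response association may partly or wholly reflect the starting level, with reversed sign, whenever the slope of follow-up on baseline is below 1. With 45 to 60 NAC patients, equal variances, correlation 0.3 to 0.7 and a baseline odds ratio of 1.5 to 2.5 per SD, the unadjusted tests are significant in about 8% to 39% of trials in which change adds nothing, against about 4% to 6% after adjustment. All of these values are assumptions, and the excess is nil at slope 1. The documents do not support saying that baseline is definitely omitted, that a misleading result will occur, or that the Wilcoxon test is invalid. The consequence is moderate, but the change is concrete and cheap enough to be worth making.

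**What to change.** In the logistic regressions of histological response on marker variation, include the baseline value of the same marker, on the log scale for concentrations and ratios. Base any statement that the change itself is related to response on that adjusted coefficient, and say in the report that it equals the effect of the end-of-NAC value given baseline. Report the Wilcoxon test on raw change as descriptive. Apply the same rule at the look after 30 patients.

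The cost is a sentence or two in the analysis plan, one extra parameter per model and a slightly wider interval in a small subgroup. No new data are needed: blood is drawn at diagnosis and TILs are read on the pre-treatment biopsy. The article reports two patients recruited when it was written, so at that stage the rule could be fixed before any response data were examined.

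### The RNA signature is a continuous prognostic score, but the indices named to verify it need the score cut into classes, which discards ranking information and ties the result to one threshold

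*Protocol article*

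**What the plan says.** Three places in the protocol article bear on this.

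- Study Design describes how the signature is computed from six genes: "The expression level of each gene will be multiplied by the corresponding coefficient in order to generate a prognostic score". The product is a number on a continuous scale. The article gives no cut-off.
- Table 1 under Study Objectives states the aim: "To verify prognostic value of a baseline RNA signature".
- Secondary Analysis says the signature will be assessed by "applying a previously constructed model on the data obtained in the INSTIGO study", and then: "The classical indices for the evaluation of a classification (sensitivity, specificity, and precision, among others) will be calculated".

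The same section assigns Wilcoxon-Mann-Whitney tests and logistic regression to TILs, NLR, PLR and ctDNA. The RNA score is not named for either.

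The protein profile is in a different position. Primary Analysis says that "in the absence of a test dataset the performance of the model can only be estimated by cross-validation".

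**The concern.** The objective concerns a score, and the stated analysis concerns a classifier. Sensitivity, specificity and precision describe one cut. They do not show whether patients further up the scale relapse more often, which is what prognostic value of a score means.

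Two consequences follow. First, the ordering of patients within each class is thrown away, in a sample expected to hold only about 30 relapses. Second, the result depends on where the cut falls on the INSTIGO measurement scale. If the RT-qPCR level differs from that of the earlier data, the indices move even though the score may rank patients just as well.

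The signature is the only model fixed beforehand and then tried on new patients, so this is where the study comes closest to confirming something.

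**Working it through.** **1. Inputs.** From Sample Size Calculation: 90 patients, "assuming that the proportion of metastatic relapses at 5 years will be 1/3", hence 30 relapses and 60 non-relapses. Not in the article, and assumed here: a normally distributed score with equal spread in both groups, a standardised difference d from 0.3 to 1.0 (AUC = Φ(d/√2), that is 0.58 to 0.76), two-sided 5% tests, and a cut that classes a half, a third or a quarter of patients as high.

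**2. The plan's own figure.** The only precision stated is ±12% for a sensitivity of 90%. Wilson interval with n = 30, p = 0.9, z² = 3.84:

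- centre = (0.9 + 3.84/60)/(1 + 3.84/30) = 0.855
- half-width = 1.96·√(0.09/30 + 3.84/3600)/1.128 = 0.111

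The interval is 74.4% to 96.5%, a half-width of 11.1 points. This agrees with the stated rough figure to within about 1 point and confirms the 30 relapses as its basis.

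**3. What the indices can and cannot show (no effect size needed).** A score unrelated to relapse that classes 90% of patients as high has sensitivity 90%, specificity 10% and precision 27/81 = 1/3, which is simply the relapse rate. Sensitivity alone therefore proves nothing. Sensitivity and specificity together do carry information, but for that cut only.

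**4. Dependence on the cut.** Take d = 0.6 (AUC 0.664) with half of patients classed high. The cut lies 0.197 SD above the non-relapse mean: sensitivity Φ(0.403) = 66%, specificity Φ(0.197) = 58%. Suppose, as an assumption, that every INSTIGO score is shifted up by 0.5 SD for assay reasons. Sensitivity becomes Φ(0.903) = 82% and specificity Φ(−0.303) = 38%. The AUC is still 0.664.

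**5. Information lost, expressed as power.**

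- Full scale: Φ(d/√(1/30 + 1/60) − 1.96). For d = 0.6: Φ(0.6/0.2236 − 1.96) = Φ(0.723) = 76.5%.
- Cut score: with p₁ and p₂ the shares above the cut among relapses and non-relapses, Φ((p₁ − p₂ − 1.96·SE₀)/SE₁). SE₀ uses the pooled proportion and SE₁ the separate ones. For d = 0.6 and a half classed high, p₁ = 0.656, p₂ = 0.422, SE₀ = 0.1118, SE₁ = 0.1076, giving 55.7% before rounding of inputs. The loss is 20.8 points.

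Power in %, with the loss in points (from unrounded values) in brackets:

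| AUC | Full scale | Half high | Third high | Quarter high |
|---|---|---|---|---|
| 0.58 | 26.8 | 18.3 (8.5) | 18.6 (8.2) | 17.9 (8.9) |
| 0.64 | 60.9 | 41.8 (19.0) | 42.2 (18.7) | 40.2 (20.7) |
| 0.66 | 76.5 | 55.7 (20.8) | 55.9 (20.6) | 53.2 (23.3) |
| 0.69 | 87.9 | 69.0 (18.9) | 68.9 (19.0) | 65.8 (22.1) |
| 0.71 | 94.7 | 80.2 (14.5) | 79.9 (14.8) | 76.7 (18.0) |
| 0.76 | 99.4 | 94.2 (5.2) | 93.8 (5.6) | 91.4 (8.0) |

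**6. Cross-checks.**

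- Simulating Mann-Whitney against chi-square (20,000 runs per effect size), with the top 45, 30 or 23 of the 90 patients classed high, gave losses of about 6 to 24 points over the same AUC range.
- These are not hard bounds. The chi-square test is discrete, and classing 22 instead of 23 patients as high raised the largest loss to about 28.
- A Cox-type approximation, Φ(√30·ln HR − 1.96) against the same with 30·2/π in place of 30 for a median split, loses 1.9 to 19.3 points for hazard ratios of 1.3 to 2.5 per SD.
- The logistic analogue, with 90·(1/3)·(2/3) = 20 in place of 30, loses about 6 to 19 points for odds ratios of 1.3 to 2.5 per SD.

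The direction is the same throughout. The size depends on the assumptions.

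**The case against.** The strongest reply has four parts.

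**No test is planned.** The article says the indices will be calculated. It gives no hypothesis test, error level or effect size for the RNA signature. This stands. A reader might infer that the trial forfeits a definite amount of power, or that a score that does predict relapse will be declared unverified. The article supports neither: the power comparison sets two unplanned tests side by side, and there is no pass/fail rule.

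**The list of indices is open-ended, and the article is condensed.** An AUC may be intended, and the cut-off may be in the full protocol or the SAP. Silence on the cut-off is therefore no fault. But the list is introduced as indices for evaluating a classification, and every index named is of that kind. The open ending commits the plan to no analysis of the score itself.

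**A locked decision rule can legitimately be validated as a classifier.** This is true, and it is why the indices should stay. Nothing in the text suggests that the cut will be chosen again on INSTIGO data. But Table 1 asks about prognostic value, which is broader than performance at one cut.

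**The analysis may not be an external validation, nor a simple high/low split.** A reader might infer both. The Introduction says the signature was established at a named centre without describing the cohort, and INSTIGO is single-centre, so independence cannot be settled from the text. The number and naming of the classes are not stated either.

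**Conclusion.** The mismatch holds: the signature is a continuous score, the objective is its prognostic value, and the only indices named require classes, while comparable markers in the same section keep their full scale. The cost is lost ranking information and dependence on one threshold, in the only analysis that carries a pre-built model to new patients.

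As an illustration only, the loss is roughly 5 to 24 points of power for AUC 0.58 to 0.76, and it is largest near AUC 0.66. Only the 30/60 split comes from the article. The normal score, effect sizes, cuts and two-sided 5% tests are assumptions.

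This is a worthwhile and cheap improvement to a secondary objective of an exploratory study. It does not touch the primary analysis.

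**What to change.** In Secondary Analysis, make the continuous score the main RNA analysis:

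- apply the original coefficients without refitting;
- report the AUC (or C-index) with a 95% confidence interval;
- report the association with relapse per 1-SD increase in the score.

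Keep sensitivity, specificity and precision as secondary descriptive results at the cut-off locked from the earlier model, not chosen again on INSTIGO data. If the full protocol or SAP already contains these analyses, one sentence in this section saying so is enough.

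With 30 relapses and 60 non-relapses, the Hanley-McNeil half-width of the 95% interval is about 0.12 at an AUC of 0.70 and 0.105 at 0.80, so the precision is similar to what the plan already accepts for sensitivity.

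The cost is a few lines of wording and one or two more reported results. No extra patients, samples or assays are needed, because the score is computed anyway. Trial Status reports 2 patients recruited at the time of writing, so the choice could be fixed well before outcome data matured.
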